| **2** | **Scientific justification and general description of the research**  The 3I method (individual, intensive and interactive) is a method of developmental management of autism and pervasive developmental disorders, originally inspired by the program Son-Rise ®, developed by AEVE when The HAS (Haute Autorité de Santé: Health Hight Authority) in March 2012 ranked this method as a non-recommended method in the absence of expert consensus and scientific assessment. The HAS however expressed the wish, that innovative methods, namely the 3I method, be the subject of clinical evaluations.  The "medical device" to be evaluated consists of support of the child (or teenager) in a playroom taking into account the sensory particularities of the child to facilitate the possibility of an exchange. For the most part the support is done by nonprofessional volunteers. Volunteers are trained in the 3I method, both before the start of the care, and during monthly experience-sharing meetings, in the presence of parents, and a professional psychologist. – fully trained to the 3I method and approved by AEVE.  The play-therapy sessions, lasting one and a half hours, two in the morning and at least two in the afternoon, putting the child in contact with about thirty volunteers during the week. The sessions are child-friendly and non-directive, but the volunteers are aware of ongoing developments that they need to make. As for the therapy sessions of exchange and development (developed by [name] at the University Hospital of Tours), these are individual play sessions with the child in which the key words for the attitude of stakeholders are: "serenity, availability, reciprocity".  The support lasts two to three years and includes steps (or phases) described in the attached INPI Filing Brochure (AEVE1 DEC1 PJ1) |
| **2.1.a** | **The intended purpose of the medical device or in vitro diagnostic medical device, if applicable specified in the instruction leaflet or instructions for use, and that provided for research:** not applicable |

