| 4.2 | **Description of the research methodology, accompanied by its schematic presentation:**  Evaluating a method involves making objective comparisons before, during and after its application. To measure the impact of the 3I method on the development of the child with autism spectrum disorders, we will compare the status of the group and each subject in the group before and after the intervention. Several evaluations will be conducted over 2 years as needed (reported in terms of significant change by volunteers) but not more than 4 to avoid the effects of repeat testing.  As shown in Figure 1, the study will last during a two-year period per included child from the pre-inclusion period.   \|  \| Pre-  inclusion \| Assessment T0  (+1month) \| Assessment T1  (+12 months) \| Assessment T2  (+24 months) \| \| --- \| --- \| --- \| --- \| --- \| \| Informed consent \| x \|  \|  \|  \| \| Inclusion criteria \| x \|  \|  \|  \| \| ADI-R \| x \|  \|  \| x \| \| CARS \| x \| x \| x \| x \| \| VABS \|  \| x \| x \| x \| \| PEP-R \|  \| x \| x \| x \| \| IMITATION \|  \| x \| x \| x \|   **Pre-inclusion period:** The recruitment of the subjects will be done on the basis of the criteria of inclusion previously established. AEVE will be responsible for obtaining the diagnostic assessments (ADI-R and CARS) of the children who will be included in the study and will obtain informed consents from the responsible parents of the child. Each parent will be informed of the study by an information leaflet (see information leaflet) and may ask all questions to the site investigator and scientific managers on the site. AEVE will communicate the list of subjects to the evaluation 1 month before the beginning of the trial. The psychologist will get in touch with the subject's parents for a pre-inclusion interview (checking the inclusion criteria and making an appointment for the first assessment). The first assessment will take place one month after the first day of care. This methodological choice was made to avoid the effect of novelty on evaluation sessions. This period will allow the child to become familiar with the change (individual and intensive care that can generate situations that are not favorable to the evaluations.  **Inclusion period:** The assessments will be carried out in the place of care (either at home or in Lud'éveil) individually in the usual playroom of the child or in a suitable environment for parental maintenance.  The research methodology for this inclusion period is divided into two phases.  Phase 1 concerns the test administration phase. The evaluation sessions will be recorded via cameras installed in the game room or via an audio recorder for parental interviews.  Phase 2 : archiving of records and data collection. This is an intermediate data processing that will consist of rating and transcribing the results obtained in the different tests. A video editing work (grouping different shots into a single sequence) will be needed to facilitate the coding of social-emotional behavior during the imitation sessions. A work that will be done from the Dartfish software. The expected date of commencement of inclusions is January 1, 2013 and the expected date of completion of inclusions is April 30, 2014.  After 12 months of care, a second assessment will take place under the same conditions following the same working methodology. Intermediate data processing can be done on the data collected at 1 month of management compared to those obtained at 12 months.  Concretely and given the administrative delays related to the qualification of this research (October 2013 to February 2014) and constitution and review of the data, the study will be a longitudinal study covering two years of care per child but including a retrospective part, for data relating to a period prior to the authorization of the research and a prospective part for data subsequent to this authorization.  **End of the tests:** A last assessment identical to the previous ones will take place after 24 months of care. This period corresponds to the date scheduled for the end of the tests which will be around April 30, 2016. The end of the study will be 3 months after the end of the tests, in order to have all the necessary time to complete all the tests, analyzes and write a scientific article.  **Duration of the study of a treatment:** The result of a method is expected over 2 years, as noted by the team of Tours (Barthélémy, Hameury & Lelord, 1995) or Sally Rogers, co-author Early Start Denver (Rogers & Dawson, 2012). Given the progressive recruitment of children under the 3I.  **Evaluation sites:** at the Center de Courbevoie or at home  A 3I Awakening Center in Courbevoie hosts since January 2013, 5 children with volunteers. The places of evaluation would be this center for the 5 children or at their home, for the others. The assessments will take place in the child's usual playroom or in a place suitable for parenting interviews. In order to optimize the evaluation sessions, the playroom will be designed to exclude any element likely to deconcentrate the child during the assessment (slide, swing, mirror, ...). It will be equipped with two chairs and a table, two tripod cameras and equipment necessary for the evaluation. |

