| 4.4 | **Description of measures taken to reduce and avoid analysis biases:**  Any validation raises methodological bias that are difficult to address. One of the questions investigators can act on is the inter-judge subjectivity for coding. Indeed, faced with varied profiles children with atypical behavior (which are sometimes very difficult to interpret), the quotes can vary from one judge to another. To avoid this analysis bias, an objective analysis grid will serve as a guide and a double coding will be done on the evaluation records. Thus we will proceed to a calculation of kappa coefficient to see the degree of agreement between several judges.  A key question that arises is: what to attribute a significant difference to? In two years, young children with autism change a lot, as do all children: longitudinal follow-ups indicate that children with the same initial profile diverge, with some of them making great progress while others stagnate or even regress (Pry & Darrou , 2009). To resolve this proble, since a control group could not be constituted, the evolution will be compared to the data available in the literature, notably (if possible) ongoing study also using PEP, CARS, Vineland and ADI-R (search workshop-class Preaut). It will take a massive superiority of the results of the method of 3I to be attributed as such the success eventually achieved. |
| **4.5** | **Detailed description of how to use the device:**  The implementation of the device assumes:  - The equipment of the 3I game room (file AEVE1 DEC1 PJ2)  - Research and selection of non-professional workers, mentioned in 2.1.d (there is usually a great diversity of stakeholders, each of whom brings to the child a way to play and their own aptitudes and interests most of them are women)  - The choice of a psychologist having the approval for a 3I care,  - The organization of the weekly schedule of the volunteers,  - The game in turn session in individual with the child,  - The note taking by the volunteer on the course of his session, with the possible mention of passages to be reviewed by the psychologist,  - The weekly session of the child with the psychologist,  - Holding of the monthly meeting of experience sharing, evaluation according to the developmental evaluation grid 3I skills and know-how, (file AEVE1 DEC1 PJ3) allowing a sharing of feeling and experience and to identify progress to be encouraged. |

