| **4.6** | **Expected duration of participation, chronology description:**  The total duration of participation of a child or teenager benefiting from the 3I method will be approximately 3 hours for each evaluation (1h for the Imitation session, 15 min break and 1h45h for the PEP). The total duration of the parent's participation will be approximately 3 hours for each evaluation (30min of pre-inclusion telephone interview, 1h for CARS and 1h30 for VABS). To this is added 4h maintenance for the ADI-R in pre-inclusion period (2h) and end of tests (2h). Over a period of 2 years of follow-up, the total duration of participation (of the child and the parent) in the specific assessments will be around 22 hours.  The duration of care as such (already performed routinely on many children) will be 30 to 35 hours per week over 2 years. |
| **4.7** | **Description of the definitive or temporary cessation rules:**  The dissolution or cessation of activity of the association Autisme Espoir Vers l'Ecole would constitute a case of permanent termination of this research as well as a ban on the method of 3I by the competent authorities.  The worsening observed at intermediate assessments in at least 1/3 of children, or the occurrence of serious adverse effects motivating discontinuation of treatment in ¼ of children, would motivate a decision to discontinue the study. |
| **4.8** | Measures implemented to maintain the blind and procedures for lifting the blind, the case  Due: Not applicable |
| **4.9** | **Identification of all "source" data to be collected directly in the observation books:**  The source data are: medical file, demographic data, family environment (couple or single parent, siblings, socio-economic level, academic level, health, family climate), audio and video recording of evaluations, rating, transcription and synthesis of results. |
| **5** | **Selection and exclusion of people from research** |

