| **7.2** | **Methods and schedule for measuring, collecting and analyzing evaluation parameters:**  The quantitative methods used to measure performance changes will consist in comparing the results obtained at the different assessments at different periods of care (T + 1 month, T + 12 months, T + 24 months). The collection and analysis of intermediate data will be carried out progressively as the evaluations are carried out. The first analysis will be conducted at the end of the second evaluation period (T + 12 months), we will compare the data from all these tests, at T + 1months. period T + 12 months. A second analysis will be conducted at the end of the tests to compare the performance of the method between the three measurement periods (T + 1 month vs. T + 12 months vs. T + 24 months).  Through PEP-R (Schopler, 2005), we will conduct a performance analysis based on an assessment and direct observation of the child. The analysis will focus on two types of data collected: 1) the age of global and specific development corresponding to different areas of development (Imitation, Perception, fine motor skills, gross motricity, hand-hand coordination, cognitive performance, verbal cognition) and And 2) behavioral observations (relationships and affect, play and interest in the material, sensory responses, and language) collected during the assessment sessions. This tool, which gives a global and specific level of development for each evaluated domain, makes it possible to see the homogeneity of the development. The more the development becomes homogeneous during the 2 years of care, the better the performance of the 3I method.  Via the Scale of Imitation (Nadel, 2012), we will perform a detailed analysis of socio-communicative skills. This tool makes it possible to evaluate the level of the preverbal communication, in particular that of the imitation. It consists of three scales: spontaneous imitation, recognition to be imitated and imitation on request. The analysis of the scores obtained in these three sub-scales will make it possible to better follow the effect of this method on the development of nonverbal communication in very young or non-verbal subjects. An analysis of socio-emotional behavior (CPSE) based on a behavioral coding grid will measure the impact of the 3I method on the evolution of social-emotional behaviors (positive vs. negative). The higher the imitation scores and the number of positive social-emotional behaviors increase over the 2 years of care, the better the 3I method's performance.  These tests will be accompanied by 3 semi-structured interviews with parents (ADI-R, CARS, VABS). These are multidimensional assessments of learning and dysfunctions in everyday life.  The ADI-R which is a diagnostic assessment tool focuses on the description and history of child development in the three domains: quality of social interactions, communication and language, narrow interests and stereotyped behaviors. A change in scores on this parent questionnaire might reflect the impact of the method.  CARS, which is also a diagnostic tool, will allow us to assess the intensity of autistic disorders and their evolution during the trial. The 15 domains usually disturbed in autism are evaluated there: social relations, imitation, emotional response, use of the body, use of objects, adaptation to change, visual responses, auditory responses, taste-smell-touch (responses and modes of exploration), fear and anxiety, verbal communication, nonverbal communication, level of activity, intellectual level and homogeneity of intellectual functioning and general impression. The lower the overall score during trail, the better the performance of the 3I method.  The VABS which is a social adaptation assessment tool makes it possible to analyze, through the scores converted into developmental age (referred to mean equivalent ages of the normal sample), the impact of the 3I method on the development of socialization, communication, and the autonomy of everyday life. The more the difference between the chronological age of the subject and his age of development decreases during the management, the better the performance of method 3I. |

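### Section 4.2 lets volunteer-reported change prompt evaluations against the fixed 1/12/24-month schedule, and no masking of coders to time point is planned

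*Protocol*

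**What the plan says.** **Timing.** Section 4.2 opens its schedule with: "Several evaluations will be conducted over 2 years as needed (reported in terms of significant change by volunteers) but not more than 4". Section 2 says who these volunteers are: "For the most part the support is done by nonprofessional volunteers". The rest of 4.2 fixes the times. The first assessment falls one month after care starts. For the second, "After 12 months of care, a second assessment will take place under the same conditions following the same working methodology". For the third, "A last assessment identical to the previous ones will take place after 24 months of care". Section 7.2 gives the same schedule, "T + 1 month, T + 12 months, T + 24 months", and 9.1 makes time the independent variable, with levels T0, T1 and T2.

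**Masking.** The item in 4.8 headed "Measures implemented to maintain the blind and procedures for lifting the blind" is answered as not applicable. Against coding bias, 4.4 offers an analysis grid, the statement that "a double coding will be done on the evaluation records", and a kappa coefficient. Section 4.2 says that sessions are filmed and that shots are edited together to help code socio-emotional behaviour in the imitation sessions. It does not say in what order recordings are coded or what the coders are told.

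**Outcomes.** The main criteria in 4.1.1 are the Nadel imitation scale and the Vineland communication and socialization scores. By 4.3, Vineland, CARS and ADI-R are obtained from the parents.

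**The concern.** The protocol gives two incompatible rules for when a child is assessed. Under one, the people who deliver the intervention can prompt an assessment when they perceive change. Under the other, the calendar decides. If a prompted evaluation took the place of a scheduled one, the timing of the measurement would depend on the perceived state of the child, and a before-after comparison would absorb that as gain.

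The second issue is independent of the first. A coder who expects improvement and knows that a clip comes from 24 months may score it higher. A second coder with the same expectation will agree. With no control group, such a shift cannot be told apart from an effect of 3I. The imitation scale, a main criterion, and the socio-emotional counts are the scores exposed to it.

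**Working it through.** The plan has no figure to reproduce here: 9.2 gives about 20 subjects with no effect size, SD or power.

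**Step 1: the timing statements compared.** The table in 4.2 has three full assessments (T0, T1, T2) and a pre-inclusion column with ADI-R and CARS only. If the cap of 4 counts full assessments, 4 − 3 = 1 prompted evaluation per child is possible. If it also counts pre-inclusion, 4 − 4 = 0 and the as-needed clause has no function. On either reading the sentence and the schedule need reconciling, and no section says whether a prompted result is analysed.

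**Step 2: what prompted timing could do, if it were used.** At fixed months the timing effect is zero. Suppose instead that each child's follow-up were taken at the best-perceived of K occasions, that nothing truly changes, and that the volunteers' perception correlates r with the measured state. K and r are assumptions. Simulation with 20 children per study and 20,000 studies gave:

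| K | r | Mean gain (SD of a single score) | Chance of a significant improvement |
|---|---|---|---|
| 2 | 0.3 | 0.17 | 7% |
| 2 | 0.5 | 0.28 | 14% |
| 6 | 0.3 | 0.38 | 21% |
| 6 | 0.5 | 0.63 | 50% |

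The reference value for improvement alone is 2.5%.

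**Step 3: a shared coding expectation.** Inputs: n = 20 (9.2), α = 0.05 (9.3; sidedness not stated, two-sided assumed), no control group (4.4). A paired t test of T2 against T0 stands in for the planned mixed model. The shift δ, in SDs of the change score, is assumed.

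- Critical value with 19 degrees of freedom: 2.093. √20 = 4.472. The smallest significant mean change is 2.093 / 4.472 = 0.468 SD.
- With no true change, P(p < 0.05) = 1 − F(2.093; 19, λ) + F(−2.093; 19, λ), where F is the noncentral t distribution function and λ = δ√20.

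| δ | λ | P(p < 0.05) |
|---|---|---|
| 0 | 0 | 5% |
| 0.1 | 0.447 | 7% |
| 0.2 | 0.894 | 14% |
| 0.3 | 1.342 | 25% |
| 0.5 | 2.236 | 57% |

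**Step 4: would agreement statistics show it?** Take two coders, a true score with SD 1, independent coder errors with SD 0.4, and the same shift b added by both. Their correlation is 1 / (1 + 0.4²) = 0.862 whatever b is. Simulated kappa, with scores cut at 0, is 0.661, 0.659 and 0.653 for b = 0, 0.3 and 0.5. A shared shift leaves agreement almost untouched.

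**The case against.** The case on the other side is substantial.

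- **The analysed time points are fixed.** 4.2, 7.2 and 9.1 agree on T0, T1 and T2, and nothing lets a prompted evaluation replace or move one. This stands: the trigger is an internal contradiction, and it biases the result only if prompted evaluations are used. The trigger also refers to significant change, not improvement, and 4.7 expects intermediate assessments to show worsening too.
- **A reader might infer that coders know the time point.** No section says so, and declaring blinding not applicable is a natural answer in a one-arm study. Section 7.2 has data collected and analysed progressively, which makes chronological coding likely, but that is inference. What the documents support is that no masking is planned.
- **A reader might infer that the better of two scores is kept.** That would add 1/√π = 0.56 of the measurement-error SD, but no such rule exists. Nor do volunteers score the main criteria.
- **The link to the main criteria is partial.** The video editing is tied explicitly only to socio-emotional coding. The double coding covers evaluation records generally, but no section says that the Nadel score is derived from the edited clips. Vineland rests on parent interview, which masked coding cannot repair.
- **A null of zero change over two years is uninformative.** 4.4 itself says that children change a lot, and it bases attribution on massive superiority over literature data. This stands as a limit on the error rates in step 3. But 4.4 gives no threshold, 9.3 still declares significance at 0.05, and a shared coding shift adds to the estimated change whether or not children mature.

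**Conclusion.** The concern holds in a limited form. The volunteer trigger contradicts the fixed schedule and has no analysis rule, so the passages must be reconciled. Separately, the plan omits masking of coders to time point, although filming and double coding are already planned, and its one agreement check cannot detect a bias that both coders share. Together these leave a route by which expectation could inflate the imitation and socio-emotional gains. They do not show that it will.

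The sizes are illustrations. The rates of 14%, 25% and 57% rest on assumed shifts of 0.2, 0.3 and 0.5 SD, n = 20, a two-sided test and no true change. The timing figures also require prompted evaluations to displace scheduled ones, which the protocol does not provide for. No figure in the protocol needs correcting. The masking part is an inexpensive improvement.

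**What to change.** **Section 4.2.** Delete the clause that makes evaluations depend on need and on volunteers' reports, or state that prompted evaluations stay outside the main analysis. Analyse T0, T1 and T2 at the actual months of care. Keep the premature-exit tests of 5.3 and 9.5: a rule admitting only on-schedule assessments would discard them, and 9.5 itself warns of bias from children who leave because they progress too little.

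**Section 4.8.** Replace the present answer with a masking rule for the recordings used in imitation and socio-emotional coding:

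- Each recording carries a random code, with date and time point removed.
- The already planned coders score the recordings in random order without being told the time point.
- For the T1 analysis, T0 and T1 form one mixed batch.
- After T2, all time points of each child are mixed and coded for the final analysis, with T0 and T1 recoded. Otherwise the late clips would be identifiable as T2.

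**Interpretation.** State that Vineland, CARS and ADI-R are parent-reported and unmasked, and interpret them accordingly.

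**Cost.** Wording, a coding list and some recoding; no additional coder is needed. Final coding waits for T2. Masking is partial, because children visibly age and a coder who administered the test may recognise the session.
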